## Abstract

Background: This methodological paper presents both a scientific rationale and a methodological approach for investigating the effects of resveratrol supplementation on mood and cognitive performance in postmenopausal women. Postmenopausal women have an increased risk of cognitive decline and dementia, which may be at least partly due to loss of beneficial effects of estrogen on the cerebrovasculature. We hypothesise that resveratrol, a phytoestrogen, may counteract this risk by enhancing cerebrovascular function and improving regional blood flow in response to cognitive demands. A clinical trial was designed to test this hypothesis. Method: Healthy postmenopausal women were recruited to participate in a randomised, double-blind, placebo-controlled (parallel comparison) dietary intervention trial to evaluate the effects of resveratrol supplementation (75 mg twice daily) on cognition, cerebrovascular responsiveness to cognitive tasks and overall well-being. They performed the following tests at baseline and after 14 weeks of supplementation: Rey Auditory Verbal Learning Test, Cambridge Semantic Memory Battery, the Double Span and the Trail Making Task. Cerebrovascular function was assessed simultaneously by monitoring blood flow velocity in the middle cerebral arteries using transcranial Doppler ultrasound. Conclusion: This trial provides a model approach to demonstrate that, by optimising circulatory function in the brain, resveratrol and other vasoactive nutrients may enhance mood and cognition and ameliorate the risk of developing dementia in postmenopausal women and other at-risk populations.

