### 2.2. Study Population

Healthy postmenopausal women from the general public residing in the Hunter region of New South Wales were invited to participate following expressions of interest to approved newspaper and radio campaigns. Each volunteer was first provided with an information statement outlining the study objectives and procedures. A health and lifestyle questionnaire that collected information pertaining to their menopausal status, medication and dietary supplement use and current perception of their cognitive status was completed by interested parties. Upon returning the questionnaire, a study investigator pre-screened volunteers via telephone to determine their potential suitability, as described in Table 1, and to invite them in for a screening/baseline visit at the research centre. They were also encouraged to consult with their medical practitioner regarding their intention to participate in this intervention prior to their first visit. Written informed consent was obtained at start of the screening/baseline visit.

Our power calculations (G*Power) [29] showed that 74 participants would give 80% chance of detecting a statistically significant difference (*p* < 0.05) of medium effect size (standardized difference = 0.67) in cognitive performance (composite score) between Resveratrol and placebo treatments. To allow for attrition, we aimed to recruit 80 women.

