### 2.3. Investigational Product and Allocation

The active and placebo capsules were of identical appearance and supplied by DSM Nutritional Products Ltd, Switzerland. The active capsule comprised 75 mg of 99% pure synthetic trans-resveratrol. The placebo comprised several inert excipients: calcium hydrogen phosphate, microcrystalline cellulose, prosolv 50 and hydrated magnesium silicate. Two hundred capsules were each dispensed in sealed white opaque containers and containers were identifiable only by code numbers. An independent investigator who held the code list allocated participants to each treatment group based on the minimisation method [30], to minimise differences between groups in age and years since ceasing menses (obtained from their health and lifestyle questionnaires) prior to the scheduled screening/baseline visit. The first participant was allocated randomly. Containers allocated to volunteers who were subsequently deemed ineligible or did not attend the screening/baseline visit were reassigned and the allocation list adjusted accordingly. Blinding will be maintained until all data analysis has been completed.

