### 2.14. Statistical Analysis

The primary outcome is the effect of resveratrol supplementation *versus* placebo on cognitive performance, determined using a composite score of all memory tests. Treatment by time effects will be determined by analysis of variance (ANOVA), or analysis of covariance (ANCOVA) in the event of interacting variables. the process of subject allocation by minimisation will have balanced age and years since cessation of menses between groups; however other baseline characteristics such as clinic BP, basal PI, BMI, 3MS score and years of education will be considered covariates if they were significantly correlated with the primary outcome.

Treatment changes in CVR to hypercapnia and/or cognitive stimuli, improvements in physical function, mood states and quality of life will be assessed using linear regressions with false rate discovery adjustments used to minimise type 1 error. In addition, to explore the potential benefits of early intervention, the magnitude of improvement following resveratrol supplementation will be compared in early (<10 years) and late (>10 years) postmenopausal women. Statistical significance for the primary outcome is set at *p* < 0.05 and false discovery rate will be applied to secondary outcomes. Statistical analyses will be performed using SPSS version 21.0 (SPSS by IBM Inc., Chicago, IL, USA).

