## Figures and Tables

**Figure 1 nutrients-08-00150-f001:**
[figure not shown]
Consort diagram for study participants.

**Table 1 nutrients-08-00150-t001:** Eligibility criteria for the study.

Inclusion Criteria
Aged 45–85 years Postmenopausal (self-reported cessation of menses for more than 6 months) Stable current medication (unlikely to change for duration of the study)
Exclusion criteria
Currently taking HRT or alternative hormone therapy for the relief of postmenopausal symptoms or have done so in the last 6 months Breast or cervical cancer Other serious disease, such as cardiovascular disease, other cancer, kidney or liver disease or neurologic condition Smokers or currently on nicotine therapy Using insulin or warfarin therapy Clinically significant depression Currently consuming more than 4 alcoholic beverages a day Changed medication in the 3 months prior to study enrolment Clinic BP > 160/100 mmhg (determined at screening) Suspected dementia (determined at screening)

**Table 2 nutrients-08-00150-t002:** Components of the Neuropsychological test battery.

Cognitive Test & Domains	Procedure	Scoring
**RAVLT (immediate and long-term verbal memory)**	*Immediate:* The participants were required to listen to an electronic audio containing 15 nouns (list A) presented at a rate of 1 word/2 s. After the audio was played, participants were required to verbally recall the words irrespective of order (trial A1). The list was presented a further four times (trial A2-A5). A second interference list (list B) was presented in the same manner (trial B6). Immediately afterward trial B6 participants were instructed to recall all the words from list A without prompt (trial A7).	Scaled scores = raw scores − errors
		Learning = scaled total (Trials A1-A5).
		Proactive memory = scaled Trial B6.
	*Delayed:* participants performed other tasks for 20 min before being required to recall all 15 words from list A (trial A8). Participants were then provided with a sheet containing all 15 words from both list A and B as well as 20 words similar in either phonology or semantic terms (total 50 words) and required to correctly identify words from both list A and list B.	
		Retroactive interference = scaled trial A7-scaled trial A5.
	For each trial, number of errors was also recorded.	
		Delayed recall = scaled trial A8.
		Recognition = Z-score list A + Z-score list B + Z-score Errors

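### The exploratory early-versus-late analysis, as worded, compares improvement after resveratrol between non-randomised menopausal-stage groups and states no placebo contrast

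*Protocol article*

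**What the plan says.** Section 2.14 (Statistical Analysis) defines the primary outcome as a comparison of resveratrol with placebo on a cognitive composite. Its model is: "Treatment by time effects will be determined by analysis of variance (ANOVA), or analysis of covariance (ANCOVA) in the event of interacting variables".

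Later in the same section a further analysis is added "to explore the potential benefits of early intervention". There the quantity to be compared is described differently: "the magnitude of improvement following resveratrol supplementation will be compared in early (<10 years) and late (>10 years) postmenopausal women". The sentence mentions neither placebo nor an interaction between treatment and stage, and no other section supplies one. The two categories also leave a woman at exactly 10 years in neither group.

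Three other places bear on the point:

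- The Abstract says of the cognitive tests: "They performed the following tests at baseline and after 14 weeks of supplementation". Table 2 describes no alternate forms.
- Table 1 admits women aged 45 to 85.
- Section 2.3 uses minimisation "to minimise differences between groups in age and years since ceasing menses", where the groups are the treatment arms.

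**The concern.** Menopausal stage is a characteristic of the woman and is not allocated. Across a 40-year age range, a cut on years since menopause will tend to separate younger from older women. Such groups can change by different amounts over 14 weeks whatever capsule they take. They may learn differently from repeated tests, may start at different distances from the maximum score (15 words in the word list, 64 images in the naming test), or may regress to the mean to different degrees.

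The placebo arm could remove these differences, since placebo women are measured in the same way at the same visits. A comparison of change on resveratrol alone does not use it. At stake is the conclusion that the analysis was added to explore: whether starting early after menopause brings more benefit.

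**Working it through.** **Inputs from the protocol article**

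- 74 women for 80% power at a standardised difference of 0.67, p < 0.05 (Section 2.2). Two-sided testing is assumed because the sidedness is not stated.
- 80 women enrolled, 40 per arm (Section 2.4).

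**Inputs that are assumed**

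- The early/late split: even (18/19 of 37, or 20/20 of 40), and 12/28 as an uneven case.
- The differential 14-week gain between stages, δ, in SD of change: 0.2 to 0.67. The article gives neither the split nor any practice effect.

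**Step 1. The plan's own figure.** A two-sided two-sample t-test with 1:1 allocation needs 36 per arm (72 in total) for 80% power at 0.67 SD. The stated 74 (37 per arm) gives 81.1%, and 40 per arm gives 84.1%. The sample size is consistent with a two-sided resveratrol-versus-placebo comparison.

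**Step 2. What each contrast estimates.** For early (E) and late (L) women, let τ be the treatment effect and π the change that would occur on placebo.

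- Within resveratrol: E − L = (τ_E − τ_L) + (π_E − π_L).
- Within placebo: E − L = (π_E − π_L).
- Interaction (first line minus second): τ_E − τ_L.

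Only the interaction isolates effect modification. It requires that π does not depend on arm within a stage, which allocation between arms is meant to secure.

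**Step 3. Rejection rate of the within-arm test when τ_E = τ_L.** The test statistic is noncentral t with n_E + n_L − 2 degrees of freedom and noncentrality λ = δ × √[n_E n_L / (n_E + n_L)]. With 20/20, √(400/40) = 3.162, so δ = 0.5 gives λ = 1.58 on 38 degrees of freedom and a rejection rate of 33.8%. The other cases are:

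| δ (SD of change) | 18/19 | 20/20 | 12/28 |
|---|---|---|---|
| 0 | 5.0% | 5.0% | 5.0% |
| 0.2 | 9.1% | 9.5% | 8.7% |
| 0.3 | 14.4% | 15.2% | 13.5% |
| 0.5 | 31.5% | 33.8% | 29.2% |
| 0.67 | 50.8% | 54.2% | 47.3% |

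**Step 4. The interaction under the same conditions.** In 20,000 simulated trials with 20 women per cell and an equal resveratrol effect in both stages, the interaction test rejected in 5.3%, 5.0%, 4.8% and 4.8% of trials for δ = 0, 0.3, 0.5 and 0.67.

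**Step 5. Direction.** The bias equals π_E − π_L and takes its sign. If late women gain 0.3 SD more from retesting and resveratrol truly helps early women 0.3 SD more, the within-arm contrast has expectation 0.3 − 0.3 = 0, and a real early benefit is hidden.

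**Step 6. Price of the interaction.** With 20 per cell, the within-arm SE is √(1/20 + 1/20) = 0.316 SD and the interaction SE is √(4/20) = 0.447 SD, a ratio of 1.41. Power for a true interaction of 0.67 SD is about 32% (about 27% with a 12/28 split). The interaction detectable with 80% power is about 1.27 SD.

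**The case against.** The strongest objection is that the sentence is shorthand. The article often omits the comparator when it means a controlled effect. The primary aim in the Introduction asks whether resveratrol can improve cognition without mentioning placebo, and Section 2.5 speaks of participants taking resveratrol capsules although half receive placebo. On that reading, improvement means improvement over placebo, and the model would be set out in an analysis plan that is not shown. This is possible, so a reader should not infer that the investigators have decided to discard the placebo arm. But nothing in the sentence says that a placebo difference is meant. It names a quantity and a comparison, and followed as written it yields an uncontrolled contrast. If the controlled contrast was intended, the wording still needs correcting.

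The following limits also stand:

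- The analysis is exploratory, has no stated decision rule and plays no part in the sample size.
- The article gives no evidence that retest gain differs by stage. The sizes and splits above are illustrations.
- A reader might infer that the bias must favour early women. It need not: younger women nearer a ceiling would gain less, which pushes the other way.
- The sentence names no outcome. Retest gain concerns mainly the cognitive scores and does not carry over directly to cerebrovascular responsiveness or the questionnaires. Regression to the mean could still act there, but it was not simulated.
- Section 2.3 contains no error. Balancing the arms on age and years since menses supports a placebo-controlled comparison by stage. It does not make early and late women comparable with each other.

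False discovery rate control, which Section 2.14 applies to secondary outcomes, does not answer the point, because the problem is bias and not multiplicity.

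**Conclusion.** The point holds for the wording of the early-versus-late analysis and goes no further. As stated, that contrast cannot separate a difference in treatment effect from a difference in change that would have occurred anyway. With an even split and no true effect modification, assumed differential gains of 0.2, 0.3 and 0.5 SD raise the false-positive rate from 5% to about 9%, 14-15% and 31-34%. The interaction stays at about 5%. The mechanism follows from the wording, whereas the size and direction in this trial are unknown.

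A reader might infer that the trial's main result is compromised. The document does not support that: the primary analysis is defined against placebo and is untouched. Nor is a false early benefit shown to be likely. What is shown is that the contrast as worded gives no protection against one, or against missing a real one.

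**What to change.** Replace the sentence in Section 2.14 with wording such as: *As an exploratory analysis, a treatment-by-menopausal-stage interaction (up to and including 10 years, or more than 10 years, since menses ceased) will be fitted in all randomised women. The early-minus-late difference in the resveratrol-minus-placebo change will be reported with its 95% CI.* Placing women at exactly 10 years in the early group is a convention; either group will do if it is fixed in advance. Continuous years since menopause may be added as a sensitivity analysis, but it assumes a linear trend and need not replace the plan's own categories.

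The change is to wording only. Placebo women are assessed identically, and years since menses is already recorded and used in the allocation, so no new data are needed. The cost is the loss of precision in Step 6: the interval will be wide, and a non-significant interaction should not be read as evidence that timing is unimportant.

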## 3. Conclusions

We have identified postmenopausal women as a vulnerable population at increased risk of cognitive decline and dementia who may benefit from supplementing their diet with resveratrol. This paper provides a rationale for investigating the effects of resveratrol supplementation on cognitive performance and mood in postmenopausal women based on our hypothesis that resveratrol can augment both by enhancing cerebrovascular perfusion. According to our hypothesis, any improvements in cognition will be secondary to improvements in CVR; however, the technical limitations of obtaining reliable TCD ultrasound signals, particularly in older women, did not warrant the inclusion of cerebrovascular function as the primary outcome as recruitment may be limited. Nonetheless it provides a detailed study design and protocol for undertaking this investigation, utilising TCD as a novel approach to evaluate impacts of supplementation on CVR. Additionally, through this paper we have outlined a model approach for which we can establish a portfolio of evidence for the efficacy of not only resveratrol but other vasoactive nutrients in maintaining optimal circulatory function to ameliorate the risk of developing dementia.

Given that resveratrol supplements are readily available over-the-counter to consumers, the anticipated outcomes will offer a non-pharmaceutical approach for managing menopause-related symptoms and counteracting accelerated cognitive and physical decline as well as mood disorders in women postmenopausally, which can be readily implemented by clinicians and the public.

## Figures and Tables

**Figure 1 nutrients-08-00150-f001:**
[figure not shown]
Consort diagram for study participants.

**Table 1 nutrients-08-00150-t001:** Eligibility criteria for the study.

Inclusion Criteria
Aged 45–85 years Postmenopausal (self-reported cessation of menses for more than 6 months) Stable current medication (unlikely to change for duration of the study)
Exclusion criteria
Currently taking HRT or alternative hormone therapy for the relief of postmenopausal symptoms or have done so in the last 6 months Breast or cervical cancer Other serious disease, such as cardiovascular disease, other cancer, kidney or liver disease or neurologic condition Smokers or currently on nicotine therapy Using insulin or warfarin therapy Clinically significant depression Currently consuming more than 4 alcoholic beverages a day Changed medication in the 3 months prior to study enrolment Clinic BP > 160/100 mmhg (determined at screening) Suspected dementia (determined at screening)

**Table 2 nutrients-08-00150-t002:** Components of the Neuropsychological test battery.

Cognitive Test & Domains	Procedure	Scoring
**RAVLT (immediate and long-term verbal memory)**	*Immediate:* The participants were required to listen to an electronic audio containing 15 nouns (list A) presented at a rate of 1 word/2 s. After the audio was played, participants were required to verbally recall the words irrespective of order (trial A1). The list was presented a further four times (trial A2-A5). A second interference list (list B) was presented in the same manner (trial B6). Immediately afterward trial B6 participants were instructed to recall all the words from list A without prompt (trial A7).	Scaled scores = raw scores − errors
		Learning = scaled total (Trials A1-A5).
		Proactive memory = scaled Trial B6.
	*Delayed:* participants performed other tasks for 20 min before being required to recall all 15 words from list A (trial A8). Participants were then provided with a sheet containing all 15 words from both list A and B as well as 20 words similar in either phonology or semantic terms (total 50 words) and required to correctly identify words from both list A and list B.	
		Retroactive interference = scaled trial A7-scaled trial A5.
	For each trial, number of errors was also recorded.	
		Delayed recall = scaled trial A8.
		Recognition = Z-score list A + Z-score list B + Z-score Errors
**Cambridge Semantic Memory Battery (semantic memory)**	*Category fluency:* Participants were given 1 min to give as many items within a given category as they could. 8 categories were used, separated into living (animals, fruits, Birds, breed of dogs) and non-living (household items, tools, vehicles, types of boats)	Number of correct responses overall.
		As per category fluency.
	*Letter fluency:* Participants were given 1 min to give as many words as they could starting with a given letter. Letters used were F, A and S. Proper nouns were excluded.	
	*Naming*: participants were required to correctly name 64 images of common living and non-living items, presented one by one.	
		As per category fluency.
	*Category Comprehension:* Participants were read the names of 64 items and required to correctly identify each from groups of images closely related to the stimuli.	
	*Semantic Association (camel and cactus):* Participants were shown an item and must correctly identify, from a separate group of 4 items, the item that is best associated with the first.	
		As per category fluency.
		As per category fluency.
**Double Span Task (visuospatial working memory)**	14 different objects were used in this task. For each task, a random number of objects (max = 5) displayed in random positions on 4 × 4 grid. Participants were prompted to either recall positions (point to position of each object in the order they were presented) or positions and names (point to the position of each object in the order they were presented saying the name of each object verbally) in an empty grid after a 5 s delay.	“Positions” = number of each correct position in order.
		“Position and names” as per “positions” with an additional mark for each correct name in order.
		Marks were then tallied for an overall score.
**Trail Making Task (executive function and processing speed)**	*Trial A:* Participants were required to draw a continuous line connecting 25 numbers spread randomly across the page in ascending order.	Trial A and B = Time taken, errors
	*Trial B:* Participants were required to draw a continuous line alternating between numbers and letters (1,a,2,b,3,c, *etc.*) spread randomly across the page	Interference = time taken (trial B/Trial A)

## Abbreviations

The following abbreviations are used in this manuscript:

ER: estrogen receptors
eNOS: endothelial nitric oxide synthase
NO: nitric oxide
HRT: hormone replacement therapy
CVR: cerebrovascular responsiveness
BP: blood pressure
3MS: Mini Modified Mental State Examination
TCD: transcranial Doppler
MCA: middle cerebral artery
PCA: posterior cerebral artery
PI: pulsatility index
RAVLT: Rey Auditory Verbal Learning Test
TMT: Trail Making Task
POMS: Profile of Mood States
CES-D: Center for Epidemiological Studies Depression Scale
MRS: menopausal rating scale
SF-36: Short-form 36
ANOVA: analysis of variance
ANCOVA: analysis of covariance
